#### In summary:

- A Cochrane review has concluded that there is not sufficient evidence to support the use of Liposomal Bupivacaine in the management of post-operative pain. Also, further Randomised controlled trials are required due to the low quality and quantity of these studies.
- Anecdotal evidence from US and a large open label case-control study suggest clinical and cost effectiveness, with same day discharge following joint replacement being performed at several centres.
- There is a lack of evidence from appropriately designed trials of the clinical and cost effectiveness of liposomal bupivacaine in knee replacement surgery.
- This simple intervention has the potential to be both clinically and cost effective but requires further evaluation to establish its role within the setting of the NHS.

## 5. OBJECTIVES AND OUTCOME MEASURES

|           | Objectives                                                                                                                                                                                                                                                                              | Outcome Measures/Endpoints                                                                                                                                                                                                                                                                                                                                            |
|-----------|-----------------------------------------------------------------------------------------------------------------------------------------------------------------------------------------------------------------------------------------------------------------------------------------|-----------------------------------------------------------------------------------------------------------------------------------------------------------------------------------------------------------------------------------------------------------------------------------------------------------------------------------------------------------------------|
| Primary   | Evaluate the effectiveness of liposomal bupivacaine with bupivacaine hydrochloride compared to bupivacaine hydrochloride alone on post-operative recovery. Post-operative recovery will be assessed both in terms of systemic recovery as well as local recovery of the operated joint. | Quality of Recovery 40 Score at 72 hours. The QoR-40 is a six dimension validated patient reported peri-operative recovery score that has been widely used across a range of surgeries including knee replacement and assesses overall post-operative recovery[24].

Cumulative daily pain score at rest using a 0-10 VAS from 0 to 72 hours following surgery. |
| Secondary | To assess other markers of recovery both in the short term and long term.                                                                                                                                                                                                               | Mean pain score measured using a 0-10 VAS at: baseline, evening of surgery (day 0) and days 1, 2 and 3 following surgery.

Quality of Recovery 40 Score at baseline, evening of surgery (day 0) and days 1, 2 and 3 following surgery.

Cumulative opioid consumption over 72 hours.                                                                      |

|  |                                                                                                     |                                                                                                                                                                                                                                                                                                                                                                                                                                                                                                                                                                                                                                                                                                                                                                                                                                                      |
|--|-----------------------------------------------------------------------------------------------------|------------------------------------------------------------------------------------------------------------------------------------------------------------------------------------------------------------------------------------------------------------------------------------------------------------------------------------------------------------------------------------------------------------------------------------------------------------------------------------------------------------------------------------------------------------------------------------------------------------------------------------------------------------------------------------------------------------------------------------------------------------------------------------------------------------------------------------------------------|
|  | 
To evaluate the cost effectiveness compared with the current standard of care.
 
Safety
 | 
Fitness for discharge against pre-defined criteria at: evening of surgery (day 0) and days 1, 2 and 3 following surgery.
 
Functional outcome using validated, patient reported (Oxford Knee Score[25]) and qualitative (American Knee Society Score[26]) outcome scores at baseline, 6 weeks, 6 months and 1 year following surgery.
 
Cost utility analysis using patient-reported quality of life as the main outcome, obtained using the EuroQol EQ5D-5 Level questionnaire at baseline, 72 hours, 6 weeks, 6 months and 1 year.
 
Serious adverse events up to 12 months post-randomisation.
 
Related AEs up to 30 days post-surgery.
 
Intraoperative and in-patient complications, specifically cardiovascular or wound complications. . These will be recorded using the Clavien Dindo Classification [27].
 |
|--|-----------------------------------------------------------------------------------------------------|------------------------------------------------------------------------------------------------------------------------------------------------------------------------------------------------------------------------------------------------------------------------------------------------------------------------------------------------------------------------------------------------------------------------------------------------------------------------------------------------------------------------------------------------------------------------------------------------------------------------------------------------------------------------------------------------------------------------------------------------------------------------------------------------------------------------------------------------------|

206

## 207 6. TRIAL DESIGN

### 208 6.1. Summary of Trial Design

209 The trial design is a patient-blinded multi-centre, active comparator, randomised controlled two-arm  
 210 parallel group superiority trial (RCT) of liposomal bupivacaine plus bupivacaine hydrochloride versus  
 211 bupivacaine hydrochloride alone for post-operative pain in patients undergoing knee replacement  
 212 surgery. Patients will be randomised in a 1:1 ratio. The RCT design is robust and reduces any potential  
 213 bias. Patients will be blinded as to which treatment they receive. Blinding of patients is possible as they  
 214 will be under general anaesthetic for their knee replacement surgery at the time of the drug  
 215 administration. Blinding of surgeons, who administer the medication and outcome assessors is not  
 216 necessary as the primary outcome is a patient reported outcome measure.

#### 217 6.1.1. Bupivacaine Hydrochloride versus Liposomal Bupivacaine Hydrochloride

218 Previous studies have demonstrated a delay between wound infiltration with liposomal  
 219 bupivacaine and the active component, bupivacaine hydrochloride, being detected in peripheral  
 220 blood. This delay appears to be associated with a delayed onset of analgesia with liposomal  
 221 bupivacaine and has been proposed to be due to the time required for the active component to  
 222 be released from liposomes and diffuse to the site of action. Since December 2015 it has

been recommended that liposomal bupivacaine is admixed with bupivacaine and co-administered in the same syringe to enhance early postoperative analgesia [28].

Amide type local anesthetics, including bupivacaine hydrochloride, have long been used for peri-articular infiltration. Historically bupivacaine hydrochloride was the drug of choice, and whilst this still remains the standard treatment in many centres, there is an increasing trend towards using ropivacaine hydrochloride. The reason for using ropivacaine hydrochloride is based on the lower cardiac and neurological toxicity seen in ropivacaine, in comparison to bupivacaine, and not due to differences in efficacy [29, 30].

We have chosen to use bupivacaine hydrochloride for this study as this represents the active component of liposomal bupivacaine, making the comparison more applicable, with the doses stated in this study well below established safety thresholds.

Bupivacaine hydrochloride, when injected immediately before or admixed with liposomal bupivacaine, may impact the pharmacokinetic and/or physicochemical properties of the drugs if the milligram dose of bupivacaine hydrochloride solution exceeds 50% of the liposomal bupivacaine dose. The doses proposed in this trial (100 mg bupivacaine hydrochloride added to 266 mg liposomal bupivacaine) falls well below this threshold so no significant interaction is expected.

## 6.2. Number of Centres

Participants will be recruited from approximately 10 NHS hospitals throughout the United Kingdom. The number of recruiting centres may be increased as the study progresses. Any additional sites will be added via a notification of amendment form to the REC and HRA, following approval by the Sponsor.

## 6.3. Patient Participation

Patients will be involved for a maximum of 12 months post-randomisation. Post operatively, patients will be asked to complete Quality of Recovery-40 assessment daily and a visual analogue scale (VAS) pain score 0-10 on the evening of surgery (day 0) and on days 1, 2 and 3 following surgery. The analgesia requirements of each patient will be recorded. The time of surgery for the patient will be noted. The day of surgery will be called Day 0.

If the patients are discharged home prior to 72 hours postoperatively, then a phone call will be made daily to the patient to collect pain VAS and QoR-40. Pain VAS will be collected by asking the question 'How painful has your operated knee been over the past 24 hours on a scale of 0-10?' The EQ-5D-5L section of the questionnaire will also be completed over the telephone if deemed appropriate. If the patient cannot be contacted between those hours, then an additional call will be made between 2pm and 6pm and this will be noted.

Fitness for discharge will be assessed as per routine clinical care on the evening of surgery (day 0) day 1, 2 and 3 following surgery, until the patient is deemed fit for discharge. This is assessed against the following criteria:

- Ability to mobilize independently
- Pain score less than or equal to 3cm on a 10cm VAS

- Ability to straight leg raise
- Ability to bend knee to 90 degrees

Once discharged, patients will be assessed as per routine clinical care. The Central Study Office will post questionnaires to patients for completion at 6 weeks post-surgery, and at 6 months and 1 year following randomisation. The local hospital research team should encourage timely completion of questionnaires if these time points coincide with the routine follow up appointments. Assessments will include completing the Quality of Recovery 40, Oxford Knee Score, American Knee Society Score and EQ-5D-5L. In addition, an analgesic history will be taken.

A trial flowchart is provided in appendix A.

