This study is designed to assess the clinical and cost effectiveness of liposomal bupivacaine in patients undergoing knee replacement surgery. The rationale for assessing the efficacy in this population is that knee replacement is known to be a painful procedure and that poor post-operative pain management is associated with delayed mobility, knee stiffness, increased risk of Deep Vein Thrombosis (DVT) or Pulmonary Embolism (PE), increased length of stay, decreased satisfaction and poor long term functional outcome. Liposomal bupivacaine may allow early mobilisation and discharge bringing significant benefits to patients at a reduced costs to healthcare providers. Previous studies carried out in the USA are on heterogeneous groups of patients and the number of patients per intervention are small. The data from the USA on efficacy of liposomal bupivacaine is equivocal and past studies have been industry-led. The patient population, local practices, as well as perioperative managements differ in the USA and in the UK and it is important to establish whether this drug will be beneficial in the NHS to reduce length of hospital stay, improve pain scores and clinical outcomes.

In a multi-centre, patient-blinded, randomised controlled trial we will assess clinical and cost effectiveness of peri-articular liposomal bupivacaine and bupivacaine hydrochloride compared with peri-articular bupivacaine hydrochloride alone in patients undergoing knee replacement surgery within the NHS. The results of this study will be directly applicable to the 100,000 patients who undergo knee replacement surgery in the UK each year and the results will help to inform healthcare providers as well as healthcare payers about the potential role that liposomal bupivacaine has within the NHS. In addition the results of this study will provide key results and play a pivotal role in informing further surgical trials across a range of surgical specialties and surgical sites in the UK.

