#### 8.5. Subsequent Assessments & Visits

Following surgery (day 0) and the 3 days following (days 1, 2 and 3) in the evening, the following information will be collected:

- Quality of Recovery 40
- Pain Visual Analogue Scale (0-10) at rest
- Cumulative opiate use (refer to patient medical notes)
- EuroQol EQ-5D-5L

Routine clinical assessments will also occur at the in-patient stage, including assessment of fitness to discharge. This information will be recorded for trial purposes.

Once discharged, patients will be seen again as per local routine clinical care. The Central Study Office will post questionnaires to patients for completion at 6 weeks post-surgery, and at 6 months and 1 year following randomisation. The following information will be collected:

- Summary medication history (since last assessment)
- Quality of Recovery 40
- Pain Visual Analogue Scale (0-10) at rest
- Oxford Knee Score
- Clinical Assessment - American Knee Society Score
- Summary healthcare and social services use as well informal care in past period due to knee (GP visits, outpatient visits, allied healthcare contacts, hospital admissions, medications, meals on wheels, and unpaid care)
- Summary employment history (in paid employment, not in employment, time away from work or usual activities)
- EuroQol EQ-5D-5L

If the patient does not return the postal questionnaire within 7 days, another questionnaire will be posted as a reminder. Following this, if we have not received a completed questionnaire within 14 days, all patient reported data will be recorded over the telephone.

An assessment table is provided in Appendix B.

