| Primary   | Evaluate the effectiveness of liposomal bupivacaine with bupivacaine hydrochloride compared with bupivacaine hydrochloride alone on post-operative recovery. Post-operative recovery will be assessed both in terms of systemic recovery as well as local recovery of the operated joint | 
 
• Quality of Recovery 40 (QoR 40) Score at 72 hours.
 
• Cumulative daily pain score at rest using 0-10 Visual Analogue Scale (VAS) from 6 to 72 hours.
 
                                                                                                                                                                                                                                                                                                                                                                                                                                                                                                                                                                                                                                                                                                                                                                                                                                                                                                                                                                                                                       |

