## 6. ANALYSIS

### 6.1 Outcome Definitions

The **co-primary outcome measures** in this trial are the Quality of Recovery 40 score and the cumulative daily pain score both measured at 72 hours post-surgery.

Quality of Recovery (QoR) 40 score – a five dimension validated patient reported peri-operative recovery score that has been widely used across a range of surgeries including knee replacement and assesses overall post-operative recovery [19]. It consists of 40 items each of which is graded on a five-point Likert scale. Total scores are calculated by summing the individual items. QoR-40 scores range from 40 (extremely poor quality of recovery) to 200 (excellent quality of recovery) [18]. The primary time point will be 72 hours post-surgery.

This outcome will also be measured at 6, 24 and 48 hours post-surgery and at 6 weeks, 6 and 12 months post-randomisation.

Cumulative daily pain score – pain at rest will be measured using a visual analogue scale (VAS) ranging from 0 (no pain) to 10 (worst possible pain). Measurements taken as close as possible to 6, 24, 48, and 72 hours post-surgery will be included in the primary outcome assessment. This outcome will also be measured at 6 weeks, 6 and 12 months post-randomisation.

The **secondary outcome measures** in this trial are cumulative opiate use, the Oxford Knee Score, the American Knee Society Score, fitness for discharge, and the co-primary outcome measures at additional time points. The health economics outcomes in this trial include summary medication history, EQ-5D-5L, summary healthcare and social services use, and summary employment history.

Cumulative opiate use – all opioids used on evening of surgery (day 0) and days 1, 2, and 3 will be recorded and a running total of cumulative opioid use calculated. A list of acceptable opioids is provided in the trial protocol.

Fitness for discharge – this will be assessed against pre-defined criteria on evening of surgery (day 0) and days 1, 2, and 3 following surgery as per routine clinical care. Patients will be considered fit for discharge when they meet four criteria: (i) ability to mobilise independently; (ii) pain score less than or equal to 3 on a 10 score VAS scale; (iii) ability to straight leg raise; and (iv) ability to bend knee to 90 degrees. It will also be recorded whether patients were discharged, and if they were not discharged when fit for discharge the reasons for this will be collected.

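### After discharge the at-rest co-primary pain score is collected by a 24-hour recall question, so the pain AUC may mix two measures according to a post-randomisation event

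*Combined protocol and SAP*

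**What the plan says.** SAP section 2.2 (Table 1) defines the second co-primary endpoint as "Cumulative daily pain score at rest using 0-10 Visual Analogue Scale (VAS) from 6 to 72 hours". SAP section 6.1 repeats that the construct is pain at rest and takes as inputs "Measurements taken as close as possible to 6, 24, 48, and 72 hours" after surgery. Protocol section 8.5 lists the item collected on the evenings of days 0 to 3 as "Pain Visual Analogue Scale (0-10) at rest", and the assessment table in Appendix B uses the same label.

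Protocol section 6.3 sets a different procedure after discharge: "If the patients are discharged home prior to 72 hours postoperatively, then a phone call will be made daily to the patient". The pain VAS is then obtained by asking "How painful has your operated knee been over the past 24 hours on a scale of 0-10". For patients not reached in the intended hours, which the section does not state, "then an additional call will be made between 2pm and 6pm and this will be noted".

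The SAP's primary analysis (section 6.2) puts all pain scores into one repeated-measures mixed model and derives one AUC per arm. It has no flag, term or sensitivity analysis for mode of collection or wording. Discharge status enters the pain analysis only through an imputation rule for missing scores (section 6.3). SAP section 6.6 plans nothing further.

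**The concern.** The telephone question differs from the defined outcome in three ways. It is not limited to rest, it asks about a period rather than the time of assessment, and it takes a spoken number in place of a mark on a scale. A recall score at 48 hours describes hours 24 to 48, whereas linear interpolation gives that score the weight of hours 36 to 60. If pain is falling (an assumption), this alone raises recall scores relative to contemporaneous ones. The hour of the call is also unsettled, although the plan otherwise calls for evening scores.

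The trigger for the change is discharge, which happens after randomisation. The protocol's rationale (section 4) says "Liposomal bupivacaine may allow early mobilisation and discharge bringing significant benefits to patients", and one fitness-for-discharge criterion is itself a pain score. If discharge timing differs between arms, the mix of questions differs too, and neither randomisation nor patient blinding removes that. Either co-primary alone can make the trial positive (protocol section 11.1, SAP section 4.1), so an error in this one can reach the main conclusion.

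**Working it through.** **Plan's own figure.** Inputs from SAP section 3.3: standardised difference 0.33, two-sided alpha 0.025, power 90%, 1:1 allocation. n per arm = 2(2.241 + 1.282)² / 0.33² = 24.82 / 0.1089 = 228 (224 if the difference is taken as 1/3). The plan states 225, so it reproduces. Power at 225 per arm is 0.896, and 225 / 0.90 = 250.

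**AUC weights.** For linear interpolation over 6, 24, 48 and 72 hours:
- 6 h: (24 − 6)/2 = 9
- 24 h: (48 − 6)/2 = 21
- 48 h: (72 − 24)/2 = 24
- 72 h: (72 − 48)/2 = 12

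They sum to 66. The scores at 24, 48 and 72 hours, the ones most open to telephone collection, carry 57/66 = 86% of the AUC.

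**Bias formula.** Let δ be the mean excess of a recall score over an at-rest score, and g(t) the between-arm difference in the proportion discharged at time t. Then the bias in the AUC difference = δ × [9g(6) + 21g(24) + 24g(48) + 12g(72)]. If every g(t) is zero, a constant δ gives zero bias.

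**Size.** The documents give no discharge rates, pain SD or wording effect. Assume an AUC SD of 120 point-hours (120/66 = 1.8 points on mean pain), so the target is 0.33 × 120 = 39.6 point-hours.

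| Discharge gap at 6/24/48/72 h (percentage points) | δ (points) | Bias (point-hours) | Share of target |
|---|---|---|---|
| 0/0/0/0 | any | 0 | 0% |
| 0/0/0/15 | 1 | 12 × 0.15 = 1.80 | 4.5% |
| 0/5/15/15 | 0.5 | 0.5 × 6.45 = 3.2 | 8% |
| 0/5/15/15 | 1 | 1.05 + 3.60 + 1.80 = 6.45 | 16% |
| 0/5/15/15 | 2 | 2 × 6.45 = 12.9 | 33% |

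**Error rates.** These use the mean-pain scale at 225 per arm, with SE = SD × √(2/225). Let b be the AUC bias divided by 66. With bias against the intervention, power = Φ[(0.33 SD − b)/SE − 2.241].

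Assume SD 2, δ = 1, and a gap of 10 points at 48 and 72 h, 5 at 24 h and none at 6 h. The AUC bias is 1.05 + 2.40 + 1.20 = 4.65 point-hours, so b = 0.07 points. That is 4.65 / (0.33 × 2 × 66) = 11% of target. Power falls from 0.896 to 0.81, and two-sided type I error rises from 0.025 to 0.035.

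The wider grid took SD 1.5 to 2.5, δ 0.5 to 2, and gaps of 5 to 20 points at 48 and 72 h, halved at 24 h. Bias ran from 2% to 57% of target, type I error from 0.025 to 0.40, and power from 0.88 down to 0.23.

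**The case against.** The strongest reply is that the switch of question is inferred. The documents print only a label for the ward item, and the outcome is called a daily score, which could fit a 24-hour ward question. If the ward used the telephone wording, the link to discharge would go and only a contradiction with the at-rest definition would remain. This stands as a caveat. The recall wording does, however, sit in the paragraph on patients discharged early.

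A reader might infer that the primary comparison is certainly biased, and against the intervention. The documents do not support either step. The protocol says only that the drug may bring discharge forward. Calls follow actual discharge, not fitness for discharge, and the SAP records the two separately. The direction requires recall scores to exceed at-rest scores, which no section states; if they are lower and the intervention speeds discharge, the bias favours it. Section 4 of the protocol gives an average stay of 3 to 6 days, which suggests that exposure falls mainly on the later scores and makes the small end of the range plausible.

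The fallback call is at least to be noted, so timing is partly handled. None of this answers the mismatch between the defined outcome and the question asked after discharge.

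**Conclusion.** The point holds as an inconsistency in how a co-primary outcome is measured. Followed as written, the plan labels 24-hour recall scores as pain at rest and pools them with scores defined as at rest. Between-arm bias arises only if early discharge differs by arm and the two questions differ systematically. Otherwise the consequence is mixed constructs and added noise.

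Under the stated assumptions for discharge gap, wording shift and AUC SD, the bias is 0 with no gap, about 5% of the 0.33 SD target with a gap at 72 hours only, 16% with the broader gap, and 33% if the wording shift is doubled to 2 points. The sign is unknown. This should be fixed; confidence in its size is medium. The required sample size does not change.

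**What to change.** Reconcile protocol sections 6.3 and 8.5 with SAP section 6.1. Use one pain-at-rest item, with the same reference period and the same evening window, on the ward and by telephone. Record mode and time for every score.

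For recall scores already collected:
- Report the share of telephone scores by arm and time point. Where mode was not recorded, the discharge status that the SAP collects at each day gives an approximation.
- At the blinded review in SAP section 3.6, pre-specify a sensitivity analysis that reruns the mixed-model AUC with the recall scores set to missing. It assumes that these are missing at random given the observed scores and covariates, and this should be stated.
- Do not use the summary-measures AUC for this, because it excludes anyone without a 6- or 72-hour score. Do not use its imputed version either, because that assigns a score of 3 to discharged patients. Both would act selectively on patients who went home early.
- Do not adjust the primary model for mode, which is itself post-randomisation.

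The cost is one wording amendment, one CRF field and one extra analysis. A change of wording mid-trial adds a further mixture, so its date must be recorded. The planned period ends on 14 August 2021 with 12 months of follow-up, which implies that the 72-hour data were complete by about August 2020, before SAP V2.0 of December 2020. If so, the reporting and the sensitivity analysis are the parts that can still be acted on.
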